### ***Outcome measures***

Data will be collected at baseline (T0) and then at 2 weeks (T1), and 8 weeks (T2) after the intervention. Table 1 shows which outcomes measures will be measured at particular time points. Beliefs about back pain will be collected using the Back Pain Beliefs Questionnaire and fear avoidance behaviours will be collected using the Fear Avoidance Beliefs Questionnaire. Pain intensity and disability will be measured using an 11 point numeric rating scale (NRS). Demographic (age, gender, highest level of education) and pain history characteristics (duration of symptoms) will be measured at baseline only while an 11 point NRS for Global Perceived Impression of Usefulness will be used at time points subsequent to baseline to measure the usefulness of the pamphlet.

**Table 1:** Outcome measures assessed by time point.

| Instrument | T0 | T1 | T2 |
|-------------------|-----------|-----------|-----------|
| Demographics      | ✓         |           |           |
| Pain history      | ✓         |           |           |
| BPBQ              | ✓         | ✓         | ✓         |
| FABQ              | ✓         | ✓         | ✓         |
| Pain intensity    | ✓         | ✓         | ✓         |
| GPIU              |           | ✓         | ✓         |
| Disability        | ✓         | ✓         | ✓         |

Participants will be asked to provide informed consent at baseline, including their contact details and date of birth. All data will be collected using a 2 page, teleform paper questionnaire which will be de-identified but linked to person details using a unique study identifier. Data at T0 will be collected onsite at the pharmacy while follow-up questionnaires (T1, T2) will be posted to participants with a reply-paid envelope. All data will be returned to Curtin University for secure storage and analysis. Participants who do not return follow-up questionnaires will be contacted by a project officer and reminded to do so.

### ***Interventions***

Interventions will be phased in the following sequence:

**A) Control (pharmacies 1-10):** pharmacists will be asked to invite the first 12 customers who meet the inclusion criteria to participate in the study as a control (N=120). In the control arm, customers will not receive any information about self-management for LBP (i.e.; will receive ‘usual care’ only).

**B) Pamphlet only (pharmacies 1-10):** pharmacists will be asked to invite the next 12 customers, that is the next 12 customers after the control participants have been recruited, who meet the inclusion criteria, to participate in the study (N=120). In this arm, participants will receive a pamphlet from the pharmacist without any further information about self management, other than usual instructions from the pharmacist relating to medication intake, dosage and side-effects. Baseline data will be collected *prior to* the pamphlet being provided.

**C) Pamphlet with education (pharmacies 11-20):** pharmacists will be asked to invite the first 12 customers who meet the inclusion criteria to participate in the study (N=120). In this arm, participants will receive a pamphlet from the pharmacist *and* the pharmacist will review the content of the pamphlet with the participant. Information provided by pharmacists will be standardised. Baseline data will be collected *prior to* the pamphlet and further information being provided. The role of the pharmacist will be to reinforce the key messages contained in the pamphlet

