## ***Aim***

The aim of this project is to undertake an evaluation of the LBP pamphlet within a primary care context. The SPIWG will partner with Curtin University and the Pharmaceutical Society of Australia (WA) (PSA-WA) for the evaluation. The project will determine whether providing the pamphlet to individuals who visit a community pharmacy to purchase pain-relieving medications for LBP is effective in improving beliefs about LBP and minimising fear avoidance behaviours related to LBP, compared to not providing the pamphlet. A secondary aim is to determine whether providing the pamphlet with the pharmacist reiterating the key messages to the consumer is more effective than providing the pamphlet alone.

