## ***Design***

A randomized, controlled trial, consisting of 3 study arms (A, B and C), will be undertaken in partnership with 20 community pharmacies in the Perth metropolitan area. A convenience sample of pharmacies will be selected through the PSA-WA. Participating pharmacies will cover major zones of the Perth metropolitan area to represent a range of socioeconomic levels. Ten pharmacies will be involved in both the 'control' (A) and 'pamphlet only' (B) arms while a separate ten pharmacies will be involved in the 'pamphlet with education' (C) arm only. Pharmacies will be allocated to study groups randomly. Each pharmacist who participates in the workshop, will receive training from the evaluation team according to their allocated study arm and remuneration for recruitment.

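### Control (A) versus pamphlet only (B), the only contrast that isolates the pamphlet, is not randomised: A and B customers are enrolled one after the other in the same pharmacies, so arm coincides with recruitment period.

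*Supplement*

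**What the plan says.** The Design section announces: "A randomized, controlled trial, consisting of 3 study arms (A, B and C), will be undertaken". On allocation it says "Pharmacies will be allocated to study groups randomly", and it describes the sharing of pharmacies: "Ten pharmacies will be involved in both the 'control' (A) and 'pamphlet only' (B) arms while a separate ten pharmacies will be involved" in arm C only.

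The Interventions section introduces the arms as a phased sequence. In pharmacies 1-10 the first 12 customers who meet the inclusion criteria are controls. For arm B, "pharmacists will be asked to invite the next 12 customers, that is the next 12 customers after the control participants have been recruited". In pharmacies 11-20 the first 12 eligible customers form arm C. Each arm has 120 participants, and in B and C the baseline questionnaire comes before the pamphlet.

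The Aim section asks first whether giving the pamphlet "is effective in improving beliefs about LBP and minimising fear avoidance behaviours related to LBP, compared to not providing the pamphlet". It then adds: "A secondary aim is to determine whether providing the pamphlet with the pharmacist reiterating the key messages to the consumer is more effective" than the pamphlet alone.

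The Feasibility section expects each pharmacy to recruit 12 participants per four-week block, or three per week. The Analysis section specifies a 3x3 repeated-measures ANOVA with group, time point and their interaction. It has no term for recruitment period or pharmacy.

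**The concern.** Random allocation of pharmacies produces two sets: one that runs both A and B, and one that runs C. It decides nothing between A and B. Which of those two arms a customer enters depends only on when that customer arrives, and nothing in the proposal randomises customers or the order of the two blocks.

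The question about the pamphlet itself rests on this contrast. Anything that makes change over follow-up differ between the first and second dozen customers in a pharmacy goes into the A-B difference in full, in either direction, so it could create an apparent benefit or hide a real one. Two routes are specific to this design. Staff become more practised between blocks. They also know which arm they are filling when they decide whom to approach. A report calling the study randomised would lend A versus B a protection it does not have.

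**Working it through.** **1. What is randomised, contrast by contrast**

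| Contrast | Question it answers | Random element | Recruitment order |
|---|---|---|---|
| A vs B | Pamphlet alone vs nothing | None | First dozen vs second dozen, same pharmacies |
| A vs C | Pamphlet plus education vs nothing | Pharmacy | First dozen in both |
| B vs C | Education added to pamphlet | Pharmacy | Second dozen vs first dozen, different pharmacies |

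In each of pharmacies 1-10, every A customer precedes every B customer. Arm and period are therefore the same variable within A and B. A period term added to the ANOVA could not be estimated separately from the arm effect using these two arms.

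**2. The plan's own sample size**

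Inputs from Appendix 1: BBQ difference 1.9, SD 5.0, power 80%, alpha 0.05 (two-sided assumed).

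- Formula: n = 2(1.960 + 0.842)² × 5.0² / 1.9², about 109 per group by the normal approximation. The t-test solution is 109.7, which rounds up to the stated 110.
- For FABQ-phys with a difference of 1.5, the same steps give 175, or 175.4 by t-test, which rounds up to the stated 176.
- One-sided tests would give 86 and 138, which do not match.

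The arithmetic is sound. Enrolment also adds up: 10 pharmacies × 12 customers × 3 arms = 360.

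**3. What a shift between blocks would do**

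The shift b is an assumption, because the documents give no figure. It is the extra BBQ change in second-dozen customers that has nothing to do with the pamphlet. No true effect is assumed, with 120 per arm, SD 5.0 and a two-sided 5% z-test.

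- SE = 5.0 × √(2/120) = 0.645
- Rejection probability = 1 − Φ(1.96 − b/SE) + Φ(−1.96 − b/SE)

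| b (BBQ points) | b/SE | False-positive rate | b as share of 1.9 |
|---|---|---|---|
| 0 | 0 | 5.0% | 0% |
| 0.25 | 0.387 | 6.7% | 13% |
| 0.5 | 0.775 | 12.1% | 26% |
| 1.0 | 1.549 | 34.1% | 53% |

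This is a pairwise test, not the planned ANOVA, and it ignores clustering and dropout.

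**4. Timing**

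At three customers per week, pharmacies 1-10 need 24/3 = 8 weeks for A and B together. A pharmacy running C needs 12/3 = 4 weeks. The text does not say which weeks those are.

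**The case against.** The design has real protections. Running A and B in the same ten pharmacies removes fixed differences in location, socioeconomic mix and staff. All participants have a baseline measure, and the group-by-time interaction removes stable baseline differences. Enrolment is meant to be consecutive, which limits staff discretion on paper, and the blocks are adjacent and planned at only four weeks each. Residual bias therefore needs something that affects change, not just starting level. All of this stands and narrows the problem, but it does not supply a random element. Consecutive enrolment is weak protection when staff know the arm and must first identify who has back pain.

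Enrolling controls first also keeps them ahead of the pamphlet's introduction. The proposal does not give this reason, but contamination is a genuine trade-off. It is limited here, because in B the pharmacist adds nothing on self-management beyond handing over the leaflet, and the education arm is already in separate pharmacies.

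Three stronger readings are tempting and are not supported:

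- **The primary comparison is not randomised.** No comparison is labelled primary. C versus A is also pamphlet versus no pamphlet and is randomised by pharmacy, although it includes the education. The word randomised is accurate for the pharmacy allocation.
- **The true error rate is 12% or 34%.** Those figures follow from assumed shifts. Nothing in the documents shows that a few weeks' difference would move change scores by that much.
- **B versus C is shown to be confounded with calendar time.** The timing of C is unclear, which calls for clarification. It does not demonstrate harm.

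**Conclusion.** The concern holds in this form. The contrast that best answers the main aim has no random element and is inseparable from recruitment period, in a study described without qualification as a randomised trial of three arms. Treating A versus B as the main contrast is an inference from the order of the aims and from its being the only contrast that isolates the pamphlet.

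The size of any bias is unknown. Under the stated assumptions it is modest for a shift of a quarter of a point and serious for a full point. The case for change does not rest on any one of those values: the design gives no means of finding out which applies, and the planned analysis cannot recover it afterwards.

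**What to change.** **Preferred.** In pharmacies 1-10, randomise each customer to A or B. Give each pharmacy 24 sealed, numbered packs that look alike, 12 with the pamphlet and 12 without, in a permuted order prepared centrally. Open the next pack only after consent and the baseline questionnaire. This fits the existing rule that baseline precedes the pamphlet, and keeps 120 per arm and N=360.

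Costs:

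- Packing 10 × 24 = 240 envelopes and revising the Design and Interventions text.
- Some contamination risk, because pamphlets are on site while controls are enrolled and the same staff both supply and withhold them. The pharmacist training should cover this.
- If C is to be concurrent with B, its recruitment must be spread over about 8 weeks. That means 12/8 = 1.5 customers per week on average in each C pharmacy, or staggered starts, and the consecutive-enrolment rule for C would need rewording to match.

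**If the sequence is kept.** Describe A versus B as a non-randomised sequential (before-after) comparison and limit its conclusions accordingly. C versus A, recruited in the same weeks, is then the pharmacy-randomised comparison. It tests the pamphlet plus education and cannot show the effect of the pamphlet alone, so the first aim would have no randomised answer. This costs only wording.

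**In either case.** State when C recruits relative to A and B.

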### ***Analysis***

A 3x3 ANOVA with one repeated measure will be used to examine main effects for group (k=3) and time point (k=3), as well as interactions between the factors.

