## ***Participants***

Pharmacists and/or pharmacy staff will identify individuals who present to the pharmacy to purchase pain-relieving medications for LBP by:

- i) asking customers about the reason for their medication purchase or GP medicine prescription;
- ii) answering questions from customers about medication options for LBP or;
- iii) customers approaching pharmacy staff about the study in response to posters placed in the pharmacy which advertise the study.

Any pharmacy customer aged 18-70 years who is currently experiencing low back pain and has adequate understanding of written and spoken English is eligible to participate. There are no exclusion criteria for this study. Each pharmacy will recruit 12 consecutive customers who meet the inclusion criteria for each study arm. The total sample size will therefore be N=360. Customers who are interested in participating will be asked to complete a consent form and a baseline questionnaire. The completed form and questionnaire will be sent by the pharmacy to Curtin University in a reply paid envelope.

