**Total**

**\$14,300**

***Appendix 1: Sample size estimates***

BBQ: assuming a mean change of 1.9 points (based on population response in Victoria from Buchbinder et al 2001), STDEV 5.0 (based on WA survey) and 80% power and alpha 0.05, sample of 110 per group needed (N=330).

FABQ-phys: assuming a mean change of 1.5 points (based on population response in Victoria from Buchbinder et al 2001), STDEV 5.0 (based on WA survey) and 80% power and alpha 0.05, sample of 176 per group needed (N=528).

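### The 3x3 ANOVA has no pharmacy term although pharmacies are the allocated unit, so standard errors for comparisons with arm C are too small whenever the quantity compared is correlated within pharmacy

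*Supplement*

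**What the plan says.** Under Design, allocation is by pharmacy: "Pharmacies will be allocated to study groups randomly". The arms do not use pharmacies in the same way: "Ten pharmacies will be involved in both the 'control' (A) and 'pamphlet only' (B) arms while a separate ten pharmacies will be involved" in arm C. Under Participants, "Each pharmacy will recruit 12 consecutive customers who meet the inclusion criteria for each study arm", and "The total sample size will therefore be N=360", which is 120 per arm. Under Interventions, arm B is filled with "the next 12 customers after the control participants have been recruited", so A and B are successive blocks in the same pharmacies. Feasibility foresees 4-week recruitment blocks.

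The Analysis section is one sentence: "A 3x3 ANOVA with one repeated measure will be used" to test the main effects of group and time, with three levels each, plus their interaction. No section shown mentions a pharmacy effect, an ICC, a design effect or cluster-robust errors. Appendix 1 sizes the trial from "BBQ: assuming a mean change of 1.9 points" with an SD of 5.0, 80% power and alpha 0.05, giving 110 per group.

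**The concern.** C versus B is the stated secondary aim, and C versus A is one of the comparisons of pamphlet with no pamphlet. Both compare one set of 10 pharmacies with another. The information about such a difference is limited by how much pharmacies differ from each other, and there are 10 + 10 - 2 = 18 degrees of freedom for estimating that. The planned ANOVA takes its between-subject error from 360 - 3 = 357 degrees of freedom among individuals.

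Correlation within pharmacy is plausible here. The pharmacies are chosen to span socioeconomic levels, staff are trained by arm, and in C pharmacists deliver part of the intervention. If it is present, p-values and intervals for C are too optimistic, and a chance difference between two sets of pharmacies could be read as an effect of pharmacist education.

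**Working it through.** **1. The plan's own sample size.** With n = 2 × SD² × (z₀.₉₇₅ + z₀.₈₀)² / δ², the BBQ inputs give 2 × 25 × (1.960 + 0.842)² / 1.9² = 108.7, so 109. The t-based version gives 109.7, so 110 as stated. FABQ-phys gives 174.4 (175) and, with t, 175.4, so 176 as stated. A one-sided version (86) and a paired version (55) do not give 110. The stated sizes are therefore two-sided comparisons of independent individuals, with no design effect.

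**2. Comparisons with C.** From the documents: m = 12 customers per pharmacy per arm, 10 pharmacies per arm, SD 5.0 (taken as the SD of the quantity compared) and complete follow-up. The ICC is assumed.

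- Naive SE = 5 × √(2/120) = 0.645.
- Design effect DE = 1 + (12 - 1) × ICC; correct SE = 0.645 × √DE.
- Real size of the nominal 5% test = 2 × [1 - Φ(1.96/√DE)].
- Power for 1.9 points uses a t-test with 18 df.

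| Assumed ICC | DE | Correct SE | Excess over naive | Real size | Power (naive 84%) | 110 × DE per arm |
|---|---|---|---|---|---|---|
| 0.01 | 1.11 | 0.680 | 5% | 6.3% | 75% | 123 |
| 0.02 | 1.22 | 0.713 | 10% | 7.6% | 71% | 135 |
| 0.05 | 1.55 | 0.804 | 24% | 11.5% | 61% | 171 |
| 0.10 | 2.10 | 0.935 | 45% | 17.6% | 49% | 231 |

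The ICC in this table is that of the quantity being compared, which differs between the two ANOVA tests.

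**3. Group main effect.** This compares each person's mean over three time points. Assume total variance 25, within-person correlation 0.5 and a constant pharmacy variance of 1.25 (ICC 0.05 at one time point). The variance of a person's mean is 1.25 + 11.25 + 12.5/3 = 16.67, so its ICC is 1.25/16.67 = 0.075. Then DE = 1 + 11 × 0.075 = 1.825 and the real size is 14.7%. A simulation of the design (4,000 runs) gave 14.8% for C versus A, with a ratio of naive to true SE of 0.73. A within-person correlation of 0.6 gives an ICC of 0.05/(0.6 + 0.4/3) = 0.068 and a size of 13.8%.

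**4. Group-by-time interaction.** This compares changes from baseline.

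- A constant pharmacy effect subtracts out. The simulation gave a size of 5.2% and a ratio of naive to true SE of 0.99 for C versus A.
- Now let pharmacies also differ in change, with variance 1 (4% of the total of 25). The change from T0 to the mean of T1 and T2 has variance 12.5/2 + 12.5 + 1 = 19.75, so the ICC of change is 1/19.75 = 0.051, DE = 1.56 and the size is 11.6%. The simulation gave 11.4% and a ratio of 0.80.

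**5. A versus B.** Let CAC be the correlation of a pharmacy's effect between its A block and its B block. The correct SE is 0.645 × √(1 + 11 × ICC - 12 × ICC × CAC), which equals the naive SE at CAC = 11/12 = 0.917.

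| Assumed ICC | Correct SE, CAC 1 | Correct SE, CAC 0.8 |
|---|---|---|
| 0.01 | 0.642 | 0.650 |
| 0.02 | 0.639 | 0.654 |
| 0.05 | 0.629 | 0.668 |
| 0.10 | 0.612 | 0.689 |

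Against the naive 0.645, the planned SE is about 0.5% to 5% too large if pharmacy effects are fully stable, and too small at CAC 0.8. In simulations where pharmacy variation in response was partly or wholly specific to each arm, the ratio of naive to true SE for the A versus B change was 0.90 and 0.78.

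**The case against.** The strongest defence is that the treatment effect lies in the group-by-time interaction. Baseline is taken before the pamphlet is given, and the sample size is expressed as a change. Stable differences between pharmacies cancel from that test, and step 4 confirms that it then keeps its 5% level. This stands: inflation of the interaction needs pharmacies to differ in change, and the documents give no figure for that. It does not clear the plan. The group main effect is also planned and is inflated by stable differences alone. In C the education comes through pharmacy staff, so differences in response between pharmacies cannot be ruled out. Standardised content may reduce them but need not remove them.

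Four stronger readings are tempting and are not supported:

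- A reader might infer that, because A and B share pharmacies, the planned A versus B standard error is simply too large. That needs pharmacy effects to be almost identical in two successive blocks, the second with a new intervention. The documents do not establish this, and the direction reverses below a correlation of 0.917.
- A reader might take 18% as the error rate of the planned interaction test. It applies only if the ICC of change is as high as 0.10.
- The sizes are two-sided, so a false finding in favour of education occurs about half as often.
- The documents do not say that one pharmacist sees all 12 customers in a C pharmacy. The argument needs only that customers share a pharmacy.

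**Conclusion.** The point holds for C versus A and C versus B. The only planned model ignores the allocated unit, and its standard errors are too small for any positive ICC of the quantity compared. The size of the error depends on an ICC the documents do not give, so the 6% to 18% is a range over assumed values of 0.01 to 0.10. For the interaction, the relevant ICC is that of change. For A versus B, the conclusion is only that the planned standard error is not reliable and that its direction is open. This should be corrected before analysis, because one of the two stated aims rests on a comparison with C.

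**What to change.** Replace the ANOVA with a linear mixed model containing:

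- fixed effects for group, time and group-by-time;
- random effects for participant, pharmacy and pharmacy-by-time;
- a random pharmacy-by-arm (block) effect, including its variation over time;
- Kenward-Roger or Satterthwaite degrees of freedom.

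The time-varying pharmacy terms are essential. A pharmacy intercept and a pharmacy-by-arm term that are constant over time both drop out of the group-by-time contrasts and would leave that test uncorrected.

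As a check that does not rely on estimating several variance components from 20 pharmacies, compare pharmacy mean changes from baseline, C versus B and C versus A, by a t-test of 10 against 10 (18 df).

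The change needs new analysis text and a pharmacy identifier in the dataset. Its cost is wider intervals and lower power for C: at an ICC of 0.05, 61% instead of 84% for 1.9 points, and 171 per arm in place of 110, against 120 planned. Appendix 1 should state power over a range of ICC. The model does not repair the A-then-B order, which is not randomised; that comparison stays open to changes over calendar time and should be described as such.

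### The planned repeated-measures ANOVA, as usually run, discards the returned forms of anyone who misses one of the two postal follow-ups

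*Supplement*

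**What the plan says.** The Analysis section of the proposal is a single sentence. It plans "A 3x3 ANOVA with one repeated measure" to test group and time point, each with three levels, together with their interaction. It names no analysis population, no treatment of incomplete records and no sensitivity analysis.

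Under Outcome measures, baseline (T0) is completed in the pharmacy, but "follow-up questionnaires (T1, T2) will be posted to participants with a reply-paid envelope", at 2 and 8 weeks. The same section foresees unreturned forms and offers one remedy: "Participants who do not return follow-up questionnaires will be contacted by a project officer and reminded to do so".

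On size, the Participants section states "The total sample size will therefore be N=360", which is 120 per arm. Appendix 1 gives "BBQ: assuming a mean change of 1.9 points" and "STDEV 5.0 (based on WA survey) and 80% power and alpha 0.05, sample of 110 per group needed (N=330"). It states no allowance for non-return.

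**The concern.** A classical ANOVA with time as the repeated factor works on complete triplets. In the common routine, a person with T0 and T1 but no T2 leaves every test, including those to which the T1 score could have contributed. The same happens to a person with T0 and T2 but no T1. A reminder may raise the return rate, but it does not change what the method does with those still missing.

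Two things are at stake. The first is precision, because data already collected and paid for go unused. The second is validity. The analysed group becomes those who returned everything, and return could well differ by arm. Controls receive no self-management material, and the only question in Section B of the T1 and T2 forms concerns a pamphlet they were not given.

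**Working it through.** **Inputs from the documents.** 120 per arm (Participants, Interventions). Appendix 1, back pain beliefs score (BBQ): difference 1.9, SD 5.0, alpha 0.05 (sidedness not stated, taken as two-sided), power 80%.

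**Assumed input.** The proportion p missing each postal form is not in the documents; 10%, 15% and 20% are shown. T0 is taken as complete.

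**Step 1: reproduce the plan's figure.** n per group = 2 × (1.960 + 0.842)² × 5.0² / 1.9² = 108.7, so 109. The t-test version gives 109.7, so 110, as stated.

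**Step 2: count usable people per arm.**
- Scores at any one wave: 120 × (1 − p).
- Complete triplets if the two forms are missed independently: 120 × (1 − p)².
- Complete triplets if the same people miss both: 120 × (1 − p).

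| p | Scores per wave | Triplets, independent | Triplets, full overlap | Loss due to method |
|---|---|---|---|---|
| 10% | 108 | 97.2 | 108 | 0 to 10.8 |
| 15% | 102 | 86.7 | 102 | 0 to 15.3 |
| 20% | 96 | 76.8 | 96 | 0 to 19.2 |

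The range assumes that missing one form does not make a person less likely to miss the other.

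**Step 3: convert to power** for a two-arm comparison at one wave, power = Φ(1.9 / (5.0 × √(2/n)) − 1.96). With all 120 it is 83.7%.

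| p | Power at the per-wave count | Power, triplets (independent) | Largest cost of the method |
|---|---|---|---|
| 10% | 79.7% (n = 108) | 75.5% (n = 97.2) | about 4 points |
| 15% | 77.5% (n = 102) | about 71% (n = 86.7) | about 7 points |
| 20% | 74.9% (n = 96) | 65.4% (n = 76.8) | about 10 points |

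Under full overlap the cost is zero. All these powers ignore clustering by pharmacy and are therefore optimistic.

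**Step 4: check the bias by simulation.** Assumptions: 400,000 people per arm, SD 5, true difference 1.9 at both waves, three correlation patterns (between-wave correlations 0.45 to 0.7), every T1 form returned, and about 70% T2 return. Where T2 return depends on the T1 score, the log-odds slope is 0.15 per point. Entries are between-arm differences in change from T0.

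| Dependence of T2 return on T1 score | Complete cases, T1 | Complete cases, T2 | Estimate valid under missing at random, T2 |
|---|---|---|---|
| None | 1.88 to 1.92 | 1.88 to 1.92 | 1.88 to 1.92 |
| Same in both arms | 1.81 to 1.83 | 1.87 to 1.90 | 1.87 to 1.91 |
| Pamphlet arm only | 2.25 to 2.37 | 1.88 to 2.09 | 1.89 to 1.91 |

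The first row shows simulation noise of about 0.02. The clear distortion is at T1 in the last row. It arises only because T1 forms already in hand are dropped when T2 is missing.

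**The case against.** **Deletion is inferred, not stated.** The Analysis sentence gives a factor structure and says nothing about incomplete records. A long-format split-plot fit would keep partial responders' rows. The document is a project proposal, and handling of missing data is often left to an analysis plan, which is not shown. This stands as far as it goes: a reader might infer that the plan prescribes listwise deletion, and it does not. But the point concerns the method named, whose usual implementation uses complete cases, and nothing in the text points elsewhere.

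**The comparison with 110 does not separate the methods.** A reader might infer that choosing ANOVA is what takes the trial below the 110 per group in Appendix 1. At 10% non-return the alternative has 108 scores per wave, also below 110. The recruitment margin (1 − 110/120 = 8.3%) is a separate matter of dropout allowance. Only the difference between the two methods counts here.

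**Overlap may remove the loss.** If the same people miss both forms, ANOVA discards nothing extra. This is right, and is why the loss is a range starting at zero.

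**Bias is not automatic.** A reader might infer that any link between earlier answers and non-return biases the result. In the simulation an equal link in both arms moved the contrast little; material bias appeared when the link differed between arms.

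**A mixed model is not a full cure.** If people stop replying because they recovered after their last form, the reason is unobserved and a missing-at-random model does not correct it. This also stands, and it is why the fix includes a shift analysis.

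**Conclusion.** The concern holds in a bounded form. The ANOVA as worded would usually be run on complete cases, and it would then waste the returned form of everyone who sent back only one of the two. With 10%, 15% or 20% missing each form, that is up to 11, 15 or 19 people per arm, and possibly none. On the BBQ inputs, the power attributable to the method falls by at most about 4, 7 or 10 points. Bias in the group contrast is possible but conditional, mainly on arm-differential dependence of non-return on earlier answers; its size varied with the correlation pattern.

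The non-return rates, overlap, correlations and return model are all assumptions, since the documents supply none of them. Confidence is high that partial responders would be lost under the usual implementation, and lower that the result would be biased. The change is worth making because a better method is available at little cost, not because the planned analysis is bound to mislead.

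**What to change.** Replace the Analysis sentence with a likelihood-based mixed model for repeated measures: arm, time and arm-by-time as fixed effects, unstructured within-person covariance, all participants analysed as allocated, and every returned form used. State that nobody is excluded for missing T1 or T2.

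Report return rates at T1 and T2 by arm. Add one sensitivity analysis that shifts unreturned scores by an amount fixed in advance, to cover non-return for reasons the returned forms do not show.

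A pharmacy random effect or adjustment for baseline would need its own justification; neither follows from this point.

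The cost is slightly more analysis work in standard software. Under Staffing, Honours students will do the analysis, so they may need some support with the model. No new data, visits or participants are required.
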